## Abstract

**Background:**

Neoadjuvant chemoradiotherapy (nCRT) followed by total mesorectal excision (TME) is the standard treatment for locally advanced rectal cancer. However, nCRT is associated with significant morbidity, impacting patients’ quality of life. Recent advancements in MRI-based risk stratification have raised the possibility of omitting nCRT in selected patients without compromising oncologic outcomes. This study aims to evaluate whether upfront TME alone achieves similar 3-year disease-free survival compared to the standard approach of nCRT followed by TME in patients with cT2N+ and cT3Nx mid-rectal cancer without MRI-based high-risk features regarding local recurrence.

**Methods:**

The CANO trial is a prospective, multicenter, observational cohort study involving 436 patients across Türkiye. Eligible patients will be classified into two groups: those undergoing direct TME and those receiving nCRT followed by TME. The primary endpoint is 3-year disease-free survival (DFS), with secondary outcomes including 5-year DFS, overall survival, local recurrence rates, and quality of life assessments using validated questionnaires. Data will be prospectively collected and monitored by the steering committee with predefined interim analyses.

**Discussion:**

The CANO trial addresses the ongoing debate regarding selective omission of nCRT in low-risk mid-rectal cancer. By leveraging MRI-based risk stratification and a collaborative national network, the study aims to provide high-quality evidence supporting a more personalized treatment approach. The findings have the potential to reduce treatment-related morbidity without compromising oncologic safety, contributing to the refinement of current guidelines.

**Trial registration:**

ClinicalTrials.gov NCT06823297 [registered before starting inclusion; Version 8, 23.06.2025].

## Introduction

Neoadjuvant chemoradiotherapy (nCRT) followed by total mesorectal excision (TME) has been the standard treatment for locally advanced rectal cancer, significantly reducing local recurrence rates [1–4], particularly in cases with threatened mesorectal fascia (MRF) or a positive circumferential resection margin (CRM) [5,6]. However, despite its oncologic benefits, nCRT is associated with considerable morbidity, including bowel dysfunction, fecal incontinence, and sexual dysfunction, which can severely impact patients’ quality of life (QoL) [2,3,7]. Additionally, with advancements in rectal cancer surgery, the necessity of nCRT for all locally advanced rectal cancer cases has been increasingly debated.

Several studies, including OCUM, MERCURY, and QuickSilver, have investigated more selective approaches to nCRT to minimize overtreatment while maintaining oncologic safety [8–10]. These studies have demonstrated that MRI-predicted negative CRM strongly indicates favorable oncologic outcomes, allowing for primary surgery without nCRT in appropriately selected patients. The OCUM trial, in particular, showed that patients with magnetic resonance imaging (MRI)-negative CRM undergoing upfront TME had an acceptably low local recurrence rate (<10%) at five years [8]. The MERCURY trial further validated MRI as a reliable tool for preoperative risk stratification, demonstrating a high accuracy in predicting negative CRM and a low risk of local recurrence in MRI-negative patients [9]. Despite these promising results, the optimal selection criteria for omitting nCRT remain a subject of ongoing research.

Current European guidelines, including those from the European Society for Medical Oncology (ESMO), advocate a risk-adapted approach to nCRT. According to ESMO, patients with cT3a/b rectal tumors located above the levator muscles, without CRM involvement or extramural vascular invasion, are considered to have a low risk of local recurrence and may be candidates for upfront surgery without nCRT [11]. This contrasts with North American guidelines, which still recommend routine nCRT for stage II and III rectal cancers [12]. However, given that modern surgical techniques have significantly reduced the risk of CRM positivity and local recurrence, a more selective approach to nCRT may be warranted.

This trial aims to investigate whether avoiding nCRT provides oncological outcomes equivalent to the standard approach in patients with locally advanced mid-rectal cancer who have a low risk of local recurrence. By leveraging MRI-based risk stratification and a real-world, multi-center cohort, this study seeks to refine patient selection criteria for nCRT and reduce unnecessary exposure to chemoradiotherapy in low-risk patients.

## Methods

### Study setting

The CANO protocol has been designed by six principal investigators (steering committee) affiliated with five tertiary referral hospitals in Türkiye (Baskent University Hospital, Istanbul Health and Technology University, Dokuz Eylul University Hospital, Halic University Memorial Sisli Hospital and Acibadem Kent Hospital) which are specialized in the treatment of colorectal cancer. The study is coordinated by the study chair (FK) from Baskent University. The steering committee includes two members responsible for writing and updating the protocol (CA, TB), two members responsible for study secretariat and communication with participant centers (IEB, OB), and two members responsible for data storage, reliability, monitoring and safety (TB, AEC).

All centers in Türkiye implementing a multidisciplinary approach to rectal cancer will be invited to participate in the study by Turkish Society of Colon and Rectal Surgery (TSCRS). The clinical administrative officer or department head of all centers will be reached by e-mail. The details of the protocol have been announced on the webpage prepared by the steering committee (https://arastirma.tkrcd.org.tr/). Centers invited to participate in the study will be informed through this website and will also receive additional information via a webinar organized by TSCRS.

In accordance with the guidelines of the Turkish Ministry of Health – Drug and Medical Devices Agency, centers that agree to participate in the study must submit a letter of support to TSCRS on behalf of the study chair (FK). This support letter must include the permission of the institutional data sharing; the signatures of the supervising researcher and clinical administrative officer/department head. Centers that submit their letters by the specified deadline (1 August 2025 anticipated) will be added to the study sites list as an update in the protocol on clinicaltrials.gov.

### Trial registration and ethical considerations

The study protocol has been prepared in accordance with SPIRIT guidelines (S1 File) and approved by Baskent University Ethical Review Board on 15-06-2025 (Approval number: KA24/461). The trial protocol has been registered before starting inclusion (NCT06823297, ClinicalTrials.gov). The study has not started patient recruitment yet and the anticipated recruitment date is 01.08.2025. The anticipated timeline is as follows: Primary recruitment completion: August, 2030, study completion: August, 2030.

Written informed consent for inclusion in the study will be obtained from all eligible patients prior to any treatment (neoadjuvant treatments or surgery), in conjunction with the treatment consents. A distinct informed consent form for the study, prepared by the steering committee and approved by the ethics committee, exists separately from the institutional informed consent form. The attending surgeon is responsible for providing the patient with comprehensive information regarding the study and securing this consent in written form. Another healthcare provider (nurse, resident, surgeon) will witness the consenting process.

In this study, participant data and biological specimens are not being collected for ancillary studies. However, each institution participating in the study may include statements in their own surgical informed consent forms regarding the use of patient information and specimens in other studies. This responsibility lies with the respective institution and the surgeon.

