### Interventions

The standard of care for the treatment of locally advanced rectal cancer is TME. In patients with cT2N+, cT3N0, and cT3N+ mid-rectal tumors, the administration of nCRT, as well as the direct TME, are both considered guideline-concordant standard treatment approaches and are widely practiced [11,12]. In this study, data from patients undergoing TME as part of routine medical care will be collected prospectively. No additional interventions, treatments and follow-up protocols outside of standard care will be implemented. At the end of the study, patients will be categorized into two groups based on whether they received nCRT and the two groups will be compared in terms of primary and secondary endpoints. No treatment or monitoring protocols differing from routine practice will be proposed for patients or surgeons in the study. The natural prognosis of the treatment arms will be observed.

All the patients undergoing TME described as a precise dissection of the rectum along with the surrounding mesorectal tissue and all pararectal lymph nodes are eligible for the study [13].

**Direct TME Group:** Patients who undergo direct TME without neoadjuvant treatment.

**nCRT Group:** Patients who receive nCRT prior to TME.

Neoadjuvan CRT treatments include all conventional chemoradiotherapy regimens or total neoadjuvant chemoradiotherapy regimens (standard short or long course radiation and/or any standard chemotherapy regimen) described in European and American guidelines [11,12]. The details of radiotherapy and chemotherapy treatments will be recorded, including dosage, frequency, duration, complications, completion status, and the waiting period between treatments. Routine follow-up information for all patients including morbidity, radiologic assessments, recurrence, mortality be recorded in the database for the first five years post-surgery. Patient-reported quality of life scales will be recorded at baseline (prior to the initiation of treatment) and subsequently at 1, 3, and 5 years.

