#### Follow-up.

Although follow-up protocols may vary among participating centers, a standardized follow-up scheme will be implemented. All patients will be monitored at regular intervals postoperatively: every three months during the first two years, every six months from years three to five, and annually thereafter. Follow-up assessments will include physical examination, serum carcinoembryonic antigen (CEA) measurement, and imaging studies (chest and abdominal CT, pelvic MRI) as per standard rectal cancer surveillance guidelines. Patient-reported quality of life will be evaluated at 1, 3, and 5 years post-surgery. All follow-up data, including recurrence, survival, and functional outcomes, will be systematically collected and entered into the study database.

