### Outcomes

#### Primary outcome measure.

3-year DFS: The proportion of patients who remain free of disease recurrence (local or distant) three years after surgical intervention. DFS will be assessed through clinical evaluations, imaging studies, and pathology reports at regular follow-up intervals.

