#### Secondary outcome measures.

5-year DFS: The proportion of patients who remain free of disease recurrence (local or distant) five years after surgical intervention.3- and 5-year Overall Survival: The proportion of patients alive at 3- and 5-years post-treatment, regardless of disease status.3- and 5-year Local Recurrence Rate: The percentage of patients experiencing tumor recurrence at the primary site (anastomosis or pelvis) within 3 and 5 years.1-, 3- and 5- year Colorectal Cancer Specific Quality of Life: Patient-reported outcomes assessed using the New Cleveland Clinic Colorectal Cancer Quality of Life Questionnaire [14].1-, 3- and 5- year Bowel Dysfunction Related Quality of Life: Patient-reported outcomes assessed using the low-anterior resection syndrome (LARS) score [15].

Fig 1 represents the timeline of anticipated recruitment and outcome measures.

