### Sample size and recruitment

The literature reports a mean 3-year disease-free survival rate of 75–85% for the sample to be included in the study [16]. For patients with mid-rectal tumors (cT2N+ and cT3N0) without high risk MRI findings, the 3-year disease-free survival rate was estimated to be 80% for both direct TME and TME following neoadjuvant chemoradiotherapy. Under these conditions, with α = 0.05 (95% confidence interval) and 80% power, the power analysis indicated that a total of 396 patients (1:1 ratio) would be required. Considering a 10% dropout rate, it is planned to include 218 patients in each group, for a total of 436 patients.

According to data from the Turkish Ministry of Health, General Directorate of Public Health, a total of 24,312 patients were diagnosed with rectal cancer between 2020 and 2024, of whom 17,896 underwent surgery (https://hsgm.saglik.gov.tr/tr/kanser.html). Since this study will be conducted nationally under the sponsorship of the main society of Turkish colorectal surgeons TSCRS, we anticipate reaching the targeted patient number within five years from the start of the study. To achieve this goal, TSCRS will utilize various channels, including mailing, social media, and its website, to announce the study and inform surgeons about the protocol.

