#### Access to data and confidentiality.

All protocols have been shared on open-access platforms including clinicaltrials.gov and the website of the trial (https://arastirma.tkrcd.org.tr/). Access to the database containing patient information will be restricted to the steering committee only. The database may be shared with authorities upon request from ethical committees and health authorities. Upon request, de-identified patient information may be shared with third parties and external researchers.

The data entered into the database by the investigators transferred to the SPSS worksheet by the study secretary and stored in a digital cloud system (Microsoft OneDrive) accessible only to steering committee and the study secretary. Consent forms will be delivered to the study secretary by the center supervisors and stored in the cloud by the study secretary. All physical and digital data collected during the study will be retained for 3 years after the completion of the study (a total of 8 years from the start of the study) and will then be permanently destroyed.

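### Recruitment and the study both end in August 2030, so the stated calendar cannot hold the 3-year and 5-year outcomes promised for all patients

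*Protocol article*

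**What the plan says.** All references are to the protocol article.

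- **Trial registration and ethical considerations:** "the anticipated recruitment date is 01.08.2025", followed by "Primary recruitment completion: August, 2030, study completion: August, 2030". Both are given as anticipated dates.
- **Sample size and recruitment:** "we anticipate reaching the targeted patient number within five years from the start of the study".
- **Primary outcome measure:** "The proportion of patients who remain free of disease recurrence (local or distant) three years after surgical intervention".
- **Secondary outcome measures:** 5-year disease-free survival (DFS) is "The proportion of patients who remain free of disease recurrence (local or distant) five years after surgical intervention". Overall survival, local recurrence and both quality-of-life measures also run to 5 years.
- **Interventions:** routine follow-up information for all patients is to "be recorded in the database for the first five years post-surgery".
- **Follow-up:** visits continue "every six months from years three to five, and annually thereafter".
- **Access to data and confidentiality:** data are to be "retained for 3 years after the completion of the study (a total of 8 years from the start of the study"), and are then permanently destroyed.
- **Adverse event reporting, safety and criteria for discontinuing:** the end of the study is tied to reaching the required number of patients, not to follow-up.
- **Statistical methods:** a Cox model is specified for time-to-event outcomes, but patients without follow-up data for the primary endpoint are excluded altogether.

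**The concern.** The timeline leaves no follow-up after the last patient is recruited, while the endpoints need three and five years from each patient's surgery. A patient operated on in August 2030 reaches the primary endpoint in August 2033 and the 5-year endpoints in August 2035. If the timeline governs, the study closes before any meaningful 5-year data exist, and with the 3-year endpoint still pending for a large share of the cohort. If the follow-up text governs, the completion date and the 8-year retention figure are wrong. The document does not say which takes precedence, and the second possibility carries a scheduled destruction of data that still belong to unfinished endpoints.

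**Working it through.** **1. The calendar's own figure.** August 2025 + 5 years = August 2030, and + 3 years of retention = August 2033, which is 8 years from the start. The retention figure therefore reproduces only if the study ends in August 2030. The two sections agree, so this does not look like an isolated slip in one date.

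**2. Share of patients with 3 years of follow-up in August 2030.** These patients must have had surgery by August 2027, within the first 2 of 5 accrual years.

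- Uniform accrual (assumption), surgery at enrolment: (5 − 3)/5 = 0.40, and 0.40 × 436 = 174 patients.
- With an assumed lag L from consent to surgery: (5 − 3 − L)/5. L = 3 months gives 0.35 (153 patients); L = 6 months gives 0.30 (131 patients).
- Other accrual shapes, with the fraction enrolled by year t taken as (t/5)^k, so that the share is 0.4^k:

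| k | Accrual | Share with 3 years | Of 436 |
|---|---|---|---|
| 2 | slow start | 16% | 70 |
| 1.5 | slow start | 25% | 110 |
| 1 | uniform | 40% | 174 |
| 0.75 | front-loaded | 50% | 219 |
| 0.5 | front-loaded | 63% | 276 |

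**3. Share with 5 years.** In August 2030: (5 − 5)/5 = 0, under any accrual shape. At the destruction date, August 2033, if follow-up had continued: (8 − 5)/5 = 0.60, or 262 of 436 under uniform accrual, and 50–55% with the 3- to 6-month lag. By then all patients could have 3 years (90–95% with the lag). The last 5-year visit would fall in August 2035, two years after destruction.

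**4. Power in August 2030.** The sample size section states no margin. A 10-point margin (the size of difference used in the stopping rule) with one-sided 5%, 80% power and 80% DFS in both groups gives

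n per group = (1.645 + 0.842)² × 2 × 0.80 × 0.20 / 0.10² = 198, so 396 in total, which is the plan's figure.

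On that same basis, with uniform accrual and no lag:

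- *Only patients with complete 3-year status:* 0.40 × 198 = 79.2 per group. Power = Φ(0.10/√(0.32/79.2) − 1.645) = 0.47.
- *Kaplan-Meier at 3 years, keeping censored patients:* with an exponential hazard giving 80% at 3 years and uniform administrative censoring, Greenwood's formula gives a variance of 0.248 per patient against 0.16 with complete follow-up. Power = Φ(0.10/√(2 × 0.248/198) − 1.645) = 0.64. Expected events within 3 years are about 56 instead of 396 × 0.20 = 79.

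**5. The alternative reading of the date.** If the first August 2030 date was meant as completion of the primary endpoint, the last surgery must be by August 2027. That conflicts with the accrual period of up to five years. Only patients operated on at the very start would reach 5 years by August 2030.

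**The case against.** The strongest reply is that the date line is merely badly worded. Its dates are anticipated, the follow-up sections commit to five years for each patient, and the Limitations section expects the study to last five years or more. Fig 1, the recruitment and outcome timeline, is not shown. It is fair to say that the investigators may intend to follow everyone for five years. But no available text gives a later end date, and the retention arithmetic repeats the five-year span. A different date in Fig 1 would add a conflict, not remove one.

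Four stronger readings are tempting, and the document does not support them:

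- *Data destruction prevents the primary endpoint.* It does not. Surgery by August 2030 reaches 3 years by August 2033. Any shortfall in 3-year DFS comes from the August 2030 completion date.
- *Most patients necessarily lack 3-year DFS at completion.* That holds for uniform or slow-start accrual. It fails if more than half of accrual falls in the first two years; five years is an upper bound and no accrual shape is stated.
- *Power falls to one low figure.* The Cox model can use censored patients, so a range is right. Switching to one-sided 2.5% lowers every value (about 35% with complete cases), but the full 396 would then give only about 70%, so comparing that with 80% is not like for like.
- *The chemoradiotherapy group is under-followed by a material amount.* Consent precedes treatment and the clock starts at surgery, so the direction is plausible. No consent-to-surgery interval is given, so no size can be attached.

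**Conclusion.** The point stands as an internal contradiction in the dates. Complete 5-year outcomes do not fit the stated calendar under any reading, and this needs no assumption about accrual or margin. The size of the 3-year shortfall does: about 40% of patients would have 3 years in August 2030 under uniform accrual, within a range of 16% to 63%. The power range of 47% to 64% rests on uniform accrual and on a margin and one-sided level inferred from the planned sample size. Data destruction in 2033 threatens the 5-year endpoints only. This should be corrected before recruitment proceeds, because destroyed data cannot be recovered.

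**What to change.** Reconcile the sections on trial registration, interventions, follow-up, secondary outcomes, sample size and recruitment, data access and discontinuation by anchoring every date to the last patient's surgery:

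- primary completion at least 36 months after it (August 2033 or later if accrual runs to August 2030);
- study completion at least 60 months after it (August 2035 or later);
- retention for 3 years from that actual completion (August 2038 or later, about 13 years from the start), replacing the 8-year total;
- in the discontinuation section, state that reaching the target number ends recruitment, not the study.

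Align the registry entry and any other study document that carries these dates. The consent form is not shown, so whether it needs changing has to be checked.

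The cost is a longer calendar, longer database hosting, and data entry and surveys at the sites over those years. No extra patients are needed, and no follow-up is added beyond what the interventions and follow-up sections already promise.

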### Trial design

The CANO trial is a prospective, non-randomized, observational, cohort study. Patients undergoing TME will be included in the study, with a comparative analysis between those receiving neoadjuvant chemoradiotherapy and those who do not. The design precludes any possibility of cross-over between the groups.

### Main question

H_0_: There is no difference in 3-year disease-free survival between direct TME and TME following nCRT in patients with mid-rectal cancer (cT2N+ and cT3Nx) without high-risk MRI findings regarding local recurrence.

H_1_: Direct TME is associated with worse 3-year disease-free survival compared to TME following nCRT In patients with mid-rectal cancer (cT2N+ and cT3Nx) without without high-risk MRI findings regarding local recurrence.

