### Statistical methods

During the study, missing data analyses and data quality assessments will be actively conducted, and measures to prevent data loss and enhance data quality will be implemented as appropriate. All statistical analyses will be conducted by experts from the TSCRS Biostatistics and Bioinformatics Analysis Unit using SPSS (SPSS Inc, Chicago, IL) software packages.

Multivariable regression analyses will be conducted to evaluate the effect of treatment strategy (direct TME vs. nCRT followed by TME) on the primary and secondary outcomes. The following covariates will be included in the models based on clinical relevance and literature review: age, sex, clinical T stage (cT2 vs. cT3), clinical N stage (N0 vs. N+), tumor differentiation, regimens of neoadjuvant treatment (long-course CRT, short-course RT, TNT with long or short-course RT), interval between neoadjuvant RT/CT and surgery, comorbidities (e.g., Charlson Comorbidity Index), performance status, postoperative complications (Clavien-Dindo), tumor histology, pathologic TME quality (pathologic completeness of the mesorectum), and center effect (as a random effect if appropriate).

For time-to-event outcomes such as disease-free survival (DFS) and overall survival (OS), Cox proportional hazards regression models will be used to estimate hazard ratios and 95% confidence intervals. The proportional hazards assumption will be tested using Schoenfeld residuals.

To address potential selection bias due to the non-randomized design, propensity score methods will be applied. Specifically, propensity scores for receipt of nCRT (vs. direct TME) will be estimated using logistic regression including the aforementioned covariates. The primary analysis will adjust for the propensity score as a covariate in the Cox model. Sensitivity analyses will be conducted using propensity score matching (1:1 nearest neighbor matching without replacement) and inverse probability of treatment weighting (IPTW) to ensure the robustness of results.

Patients lacking the main data specified in the inclusion and exclusion criteria, demographic data, or follow-up data related to the primary endpoint will be completely excluded from the study. Patients with missing data from other variables or secondary endpoints will only be excluded from those specific analyses, and secondary endpoints will be evaluated using data from patients with complete datasets.

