## Discussion

In line with current recommendations, some surgeons perform upfront TME for patients with T2-3 node-positive mid-rectal cancer in the absence of MRF involvement. However, in these cases, the common approach is to administer neoadjuvant chemoradiotherapy. This study seeks to evaluate whether upfront TME achieves non-inferior 3-year disease-free survival compared to the standard.

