## Conclusion

The CANO trial has the potential to provide pivotal evidence on the selective use of nCRT in mid-rectal cancer. If successful, the results could guide a more personalized approach to rectal cancer treatment, minimizing overtreatment without compromising oncologic outcomes. The study’s findings will not only contribute to the literature but also serve as a model for future collaborative research efforts in Türkiye and beyond.

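### The stated hypotheses test for inferiority from a null of no difference, so they cannot deliver the non-inferiority conclusion that the trial seeks and was apparently sized for

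*Protocol article*

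**What the plan says.** Main question gives the null as "There is no difference in 3-year disease-free survival between direct TME and TME following nCRT" and the alternative as "Direct TME is associated with worse 3-year disease-free survival compared to TME following nCRT", both for the MRI-low-risk mid-rectal population. No margin is attached to either.

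The aim is worded in three ways:
- Abstract, Background: "This study aims to evaluate whether upfront TME alone achieves similar 3-year disease-free survival".
- Introduction: "whether avoiding nCRT provides oncological outcomes equivalent to the standard approach".
- Discussion, opening paragraph: "This study seeks to evaluate whether upfront TME achieves non-inferior 3-year disease-free survival compared to the standard".

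The Conclusion says what a successful result would be used for: "minimizing overtreatment without compromising oncologic outcomes".

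Sample size and recruitment assumes equal rates: "the 3-year disease-free survival rate was estimated to be 80% for both direct TME and TME following neoadjuvant chemoradiotherapy". It then gives α = 0.05, with a 95% confidence interval in brackets, 80% power, and 396 patients at 1:1. This is raised to 436 for 10% dropout. It names neither a margin nor one- or two-sided testing.

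Statistical methods fixes the main comparison: "The primary analysis will adjust for the propensity score as a covariate in the Cox model". Cox models are to report hazard ratios with 95% confidence intervals. No criterion is given for calling direct TME non-inferior.

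The only 10-point figure is in the section on adverse events, safety and discontinuation, where a between-group difference above 10% in DFS or local recurrence is a reason to end the study.

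**The concern.** In a non-inferiority test the null says that the new strategy is worse by at least a margin, and rejecting it supports the claim. Main question runs the other way. Rejecting its null shows that direct TME is worse; not rejecting it shows nothing in particular. No outcome of that test establishes similarity, equivalence or non-inferiority, yet those are the aims stated in the Abstract, Introduction and Discussion.

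A non-rejection also becomes more likely as precision falls, so a less informative study is more likely to give the result that looks favourable. If that result were taken as support for omitting nCRT, a DFS loss that matters could pass unnoticed.

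The hypotheses also disagree with the sample size, which assumes a true difference of zero. The document therefore describes two different tests of its primary endpoint.

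**Working it through.** **1. Reproduce 396.** Inputs from Sample size and recruitment: 80% in each group, α = 0.05, 80% power, 1:1.

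A difference test needs n proportional to 1/(p1 − p2)². With p1 = p2 = 0.80 the denominator is zero, so no finite sample size exists.

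For non-inferiority with margin M, n per group = (z_alpha + z_power)² × [p1(1 − p1) + p2(1 − p2)] / M². The margin of 0.10 is my assumption.
- One-sided 0.05: (1.645 + 0.842)² × 0.32 / 0.01 = 197.8, so 198 per group and **396** in total. This matches exactly.
- One-sided 0.025 (lower limit of a two-sided 95% interval): (1.960 + 0.842)² × 0.32 / 0.01 = 251.2, so 252 per group and **504** in total.
- Two one-sided 0.05 tests for equivalence within 10 points: 275 per group, 550 in total.

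The 10-point reading remains an inference. At one-sided 0.025, 198 per group would correspond to a margin of about 11.3 points. The total also moves steeply with the margin: at one-sided 0.05 / 0.025 it is 1584 / 2010 for 5 points, 704 / 894 for 7.5 points and 276 / 350 for 12 points.

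**2. Error rates of the test as written.** Assume 198 per group, nCRT at 80%, direct TME at q, and an unadjusted comparison of proportions.

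P(not rejecting) = 1 − Φ(d / SE − z), with d = 0.80 − q and SE = √[(0.16 + q(1 − q)) / 198].

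For q = 0.70: SE = √(0.37 / 198) = 0.0432 and d / SE = 2.313.
- One-sided 5%: 1 − Φ(2.313 − 1.645) = 0.252.
- Two-sided 5%: 1 − Φ(2.313 − 1.960) = 0.362.

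For q = 0.75: SE = √(0.3475 / 198) = 0.0419 and d / SE = 1.194.
- One-sided 5%: 0.674.
- Two-sided 5%: 0.778.

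The alternative is directional, so the one-sided figures fit it best. Pooled-variance versions differ by no more than about half a point.

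**3. Comparison with a non-inferiority test.** With a 10-point margin, a true 10-point deficit lies on the boundary of the null. It is wrongly passed at most 5% of the time (one-sided 0.05) or 2.5% (one-sided 0.025), against 25% or 36% above. The 5-point case does not show a gain from the change, because a 10-point margin would treat a 5-point deficit as acceptable.

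**4. One observed result under both rules.** Suppose 80% against 75% is observed. Then z = 0.05 / 0.0419 = 1.19 and the null of no difference stands. The 95% interval for the deficit is 0.05 ± 1.96 × 0.0419, from −3 to +13 points. The one-sided 95% bound is 0.05 + 1.645 × 0.0419 = 0.119, or 11.9 points. Neither bound excludes 10 points, so non-inferiority would not be shown.

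**5. Power of the restated test at 198 per group.** Φ(0.10 / √(0.32 / 198) − z) = Φ(2.487 − z), which is 80.0% at one-sided 0.05 and 70.1% at one-sided 0.025.

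**6. Margin on the hazard-ratio scale.** Under proportional hazards, 80% against 70% gives ln(0.70) / ln(0.80) = 1.60.

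**The case against.** **Intent.** A reader might infer that the investigators will report a non-significant result as proof that nCRT can be omitted. The document does not say so. Hazard ratios are planned with 95% confidence intervals, which would show how large a deficit remains compatible with the data. Limitations concedes residual confounding, and the Conclusion is conditional. What stands is that the hypotheses allow the misreading and give no rule against it.

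**Power.** A reader might infer that the study is simply underpowered. That holds for the test as written (about 75% one-sided against a 10-point deficit). It does not hold for a 10-point non-inferiority test at one-sided 0.05, where 396 gives 80%.

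**A limit exists.** The termination criterion calls a difference above 10% unacceptable, so the document does contain a tolerance. It is a reason to stop the study, however, and is not tied to the hypotheses, the sample size or the primary comparison.

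**Left to the analysis plan.** A margin or decision rule could sit in a document not shown. The hypotheses, though, are stated here and conflict with the aim and the sizing here. An analysis plan with a margin would contradict Main question.

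**Scale.** The endpoint is a 3-year proportion and the analysis yields a hazard ratio. This is secondary: a Cox model can carry a non-inferiority criterion once a matching margin is set.

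**Illustration.** The error rates are unadjusted and assume exactly 198 per group. The planned analysis is adjusted, and an observational cohort cannot guarantee 1:1. The figures show the order of magnitude only.

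**Conclusion.** The point holds. The hypotheses in Main question contradict the aim in the Abstract, Introduction and Discussion, and they contradict the equal-rates sample size. This is a wrongly stated rule, not missing detail. Non-rejection of the stated null cannot support the trial's main claim.

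At 198 per group and 80% under nCRT, the stated test leaves a true 10-point deficit undetected about 25% of the time one-sided (36% two-sided). A 10-point non-inferiority test would accept it at most 5% (2.5%) of the time. These figures rest on unadjusted binomial comparisons and on a 10-point margin inferred from the exact match to 396.

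A reader might also conclude that correcting the hypotheses leaves the sample size untouched. That is so only at one-sided 0.05. The 95% confidence interval mentioned in the sample size section points towards one-sided 0.025, under which power is about 70%.

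**What to change.** 1. Restate the hypotheses as H0: DFS3(direct) − DFS3(nCRT) ≤ −M against H1: DFS3(direct) − DFS3(nCRT) > −M. The sponsor should confirm and justify M before outcome data are seen; 10 points is what 396 implies.
2. State whether alpha is one-sided 0.05 or one-sided 0.025.
3. Give the decision rule. Conclude non-inferiority only if the matching lower confidence bound of the adjusted 3-year DFS difference lies above −M, or if the upper bound of the adjusted Cox hazard ratio lies below the matching margin (about 1.60 for 80% against 70%). Choose one of the two as primary.
4. State that a non-significant difference is not evidence of similarity, and use one term for the aim throughout.
5. Align the sample size text. At one-sided 0.05, add the margin and sidedness and keep 396 with 80% power. If the two-sided 95% interval decides, either restate power as about 70% or plan for about 504 evaluable patients (504 / 0.90 = 560 with 10% dropout).

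The cost is rewording, plus more recruitment if the 95% interval decides and 80% power is kept. The article reports that recruitment had not begun, so at that point the margin could still be fixed without sight of data. The adjusted estimate also needs a usable propensity score: Statistical methods includes the neoadjuvant regimen and the interval to surgery among its covariates, and these exist only in the nCRT group. That must be settled before the rule can be applied.
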